### Statistical analysis

Data will be analysed in concordance with the Consort Cluster guide [44], and all analyses will be done on an intention to treat basis. A descriptive analysis and an analysis of baseline comparability between the study groups will be performed for the variables studied. A Student's t test or a Mann-Whitney U test will be used to compare means with two categories. An ANOVA test will be done to compare means with two or more categories, and a Chi- squared test or a Chi -squared tendency test will be done to compare categorical variables. A multilevel logistic regression will be carried out to evaluate the association between the dependent and the independent variables that were statistically significant in the bivariate analysis. All analyses will be adjusted for potential confounding factors and for variables with clinical relevance. All tests will be done with a 95% bilateral confidence interval. SPSS 15, STATA 10 and HLM6 will be used.

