### Secondary Objectives

1. Validate the questionnaire on nutritional iodine status in pregnant women.

2. Determine the iodine-rich foods consumed by pregnant women in each trimester of gestation and how these foods are prepared (boiled, fried, baked...).

3. Determine whether pregnant women use iodised salt in the preparation and condimentation of foods.

4. Determine whether pregnant women take any supplement containing iodine during gestation.

5. Describe the modifications in the smoking habits produced during gestation.

6. Compare the nutritional iodine status of the pregnant population between the different Primary Care Centres (PCC) participating in the study, ethnic groups, levels of education and gestational trimester.

7. Study the repercussions of the educational interventions on hygienic-dietetic habits and smoking as well as on iodurias and the taking of iodine supplements.

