### Sample size calculation

The sample size has been calcuated by multipying the size of a randomized simple design by the design effect. For the simple randomized design an alpha error of 0.05 and a beta error of 0.20 in a bilateral contrast are considered, requiring 204 pregnant women in the intervention group and 204 in the non intervention group to detect a difference greater than or equal to 15% in the prevalence of iodine deficiency between the two. After extensive review of the literature on group educational interventions in a pregnant population, the investigative team [37-40] considered that the intervention to be undertaken in the intervention group will achieve an improvement of at least 15% in hygienic-dietetic habits and thus in the levels of ioduria. A proportion of iodine deficiency of 44% in the non intervention group is assumed as indicated by studies performed in populations in the Pyrenees and the coast of the Maresme, areas near the study setting [18]. A loss to follow up of 15% has been estimated. Using an intracluster correlation coefficient of 0.05 [41-43], and based on an average of 25 pregnant women per PCT, the design effect is 2.2. Therefore, 898 pregnant women and 36 PCT are needed.

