### Data Collection

*Dependent Variables*: iodine deficiency (yes, no), is defined as ioduria less than 150 μg/lL

Independent Variables:

Variables related to the woman (information obtained through a individualized interview):

- Administrative: PCT, midwife, data collection date, patient code, telephone number.

- Sociodemographic: date of birth, level of education, etnia.

- Obstetric: n° of pregnancies brought to term; n° premature births, n° of miscarriges and n° of live births, trimester of gestation of the woman (1st, 2nd or 3rd).

- Related to smoking: smoker (no, yes), cigarettes/day prior to gestation, cigarettes/day during gestation, ex-smoker because of pregnancy, ex-smoker and time since cessation of smoking.

- Related to consumption of iodine-rich foods:

▪ Consumption of milk: glasses/day

▪ Consumption of yoghourt: units/week and type (whole or skimmed).

▪ Consumption of cheese: rations/week and type (cured, semi-cured and fresh).

▪ Consumption of vegetables: times/week, usual preparation (raw, fried, grilled/baked, steamed, boiled) and use of water in which they have been boiled (yes, no and no answer).

▪ Consumption of vegetables and garden produce: times/week.

▪ Consumption of fish: times/week, usual preparation (raw, fried, grilled/baked, steamed, boiled).

▪ Consumption of tinned tuna: times/week.

▪ Consumption of tinned sardines: times/week.

▪ Consumption of meat and derivatives: times/week.

▪ Consumption of eggs: units/week.

▪ Consumption of fruit: units/week and types (strawberries, pineapple, peaches, bananas, oranges and others).

▪ Consumption of nuts: times/week.

- Consumption of iodised salt: yes (time of consumption), no.

- Consumption of multiple vitamins containing iodine: yes (type), no.

- Consumption of potassium iodine supplement: yes (type), no.

- Related to the intervention: study group (intervention, non intervention), attendance to group workshop (yes, no).

Variables related to the midwife (information obtained through a individualised interview): years in the profession, primary care nursing training, mean number of visits per day.

Variables related to the PCT (information obtained through an individualised interview): population assigned, mean age of population assigned, whether or not it is a teaching center for residents, number of midwives.

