- Request for ioduria during the first trimester: the midwife will request an ioduria test and will explain the woman how to correctly collect the urine and will program the appointment for the second trimester visit of the pregnancy. On receipt of the ioduria results the midwife will note these in the EDCF. In cases in which iodine deficiency is detected the midwife will duly intervene, thus the reason for including the telephone number of the pregnant woman in the questionnaire. If iodine supplementation is indicated the administration will begin on collection of the first urine sample to avoid underestimation of the prevalence of iodine deficiency in the first trimester. Ioduria will be analysed using the Benotti&Benotti method performed in the laboratory of the Hospital Clinic of Barcelona.

* **PHASE 5. Group Education Intervention (only in IG)**: the coordinating midwives in each zone will be responsible for performing the educational workshops on hygienic-dietetic habits in the pregnant women in the intervention group. This workshop will be held in the first trimester since this is when organogenesis is produced and is therefore the time of greatest risk for the appearance of alterations in the development of the foetal central nervous system in cases of maternal iodine deficiency. The content of the educational workshop will be the same to avoid a variation in information and transmission of knowledge to the pregnant women, that is, to ensure receipt of homogeneous information by the pregnant women.

* **PHASE 6. Follow up (in IG and NIG)**: if a pregnant woman does not attend the appointment she will be called by telephone and if she cannot be contacted after 10 attempts she will be withdrawn from the study. The interview on hygienic-dietetic habits will be given in the second and third trimester appointments and determination fo ioduria will be requested. The reasons for participant withdrawal will be reported and a flow chart of the patients will be created throughout the study.

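### Iodine status is to be compared across trimesters in the same women, but the only bivariate tests named are for independent samples, so the trimester comparison would be conservative and lose some power

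*Protocol article*

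**What the plan says.** The design is longitudinal within woman. The exclusion criteria rule out women in the second or third trimester, so all participants enter in the first, when the first ioduria is requested. Phase 6 of the Description of the Study then says "The interview on hygienic-dietetic habits will be given in the second and third trimester appointments", and ioduria is requested at those visits too.

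Trimester is also something to be compared. Secondary objective 6 compares iodine status between care centres, "ethnic groups, levels of education and gestational trimester". The Data Collection section lists "trimester of gestation of the woman (1st, 2nd or 3rd") among the independent variables, with iodine deficiency (ioduria below 150 μg/L) as the dependent variable.

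For bivariate comparisons, the Statistical analysis section gives Student's t or Mann-Whitney for two categories, and continues: "An ANOVA test will be done to compare means with two or more categories, and a Chi- squared test or a Chi -squared tendency test" for categorical variables. Variables significant in these tests go into a multilevel logistic regression whose levels are not stated, with adjustment for confounders and clinically relevant variables. The only correlation quantified anywhere is that between women of the same care team (coefficient 0.05, design effect 2.2).

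**The concern.** Three readings from one woman are not three readings from three women. In the forms named, the t test, Mann-Whitney, ANOVA and chi-squared tests refer their statistic to a distribution for unrelated groups. Across trimesters the question is whether the same women change, and each woman's own stable level cancels from that contrast. A test that ignores the pairing puts that stable level back into the error term. It therefore rejects less often than its nominal 5% when nothing changes, and has less power when something does.

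At stake is the trimester part of secondary objective 6. A real change in deficiency during pregnancy could be reported as non-significant more often than the data warrant. Because bivariate significance is a route into the regression, trimester itself could also fail that screen. The problem is separate from clustering by care team and would remain after a full correction for it.

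**Working it through.** **1. The plan's own figures.** Inputs from Sample size calculation: "an alpha error of 0.05 and a beta error of 0.20 in a bilateral contrast are considered"; "A proportion of iodine deficiency of 44% in the non intervention group is assumed"; the aim is "to detect a difference greater than or equal to 15% in the prevalence of iodine deficiency between the two"; loss to follow-up 15%; intracluster coefficient 0.05; 25 women per team.

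- 44% vs 29%, with continuity correction: 174 per arm. After losses, 174/0.85 = 204.7, or 205, against the stated 204. (44% vs 59% without the correction also gives 174.)
- Design effect: 1 + (25 − 1) × 0.05 = 2.2.
- Total: 408 × 2.2 = 897.6, so 898 women; 898/25 = 35.9, so 36 teams.

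The sample size reproduces to within rounding. It concerns a between-arm comparison with one result per woman, so repeated measurement does not enter it. The design effect covers care teams only.

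**2. Inputs for the trimester comparison.** Women with complete data: 898 × 0.85 = 763. Starting prevalence: 44%. Within-woman correlation r of the yes/no result: not in the protocol; 0.1 to 0.5 is assumed, equal for every pair of trimesters. Clustering by team is left out.

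**3. True level of the three-trimester chi-squared test.** The variance of a difference between two trimesters is 2p(1−p)(1−r)/n, but the test uses 2p(1−p)/n. With no change, the statistic behaves as (1−r) times a chi-squared variable on 2 degrees of freedom. Its upper tail beyond x is exp(−x/2), so with critical value 5.99 the true level is exp(−5.99/[2(1−r)]).

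| r | exponent | true level |
|---|---|---|
| 0.1 | −5.99/1.8 | 3.6% |
| 0.2 | −5.99/1.6 | 2.4% |
| 0.3 | −5.99/1.4 | 1.4% |
| 0.5 | −5.99/1.0 | 0.25% |

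Simulation with 763 women agrees, and Cochran's Q holds about 5%.

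**4. Power, chi-squared vs Cochran's Q** (simulated, 763 women):

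| Deficiency in trimesters 1/2/3 | r = 0.2 | r = 0.3 | r = 0.5 | points lost |
|---|---|---|---|---|
| 44/36.5/36.5% | 90 vs 94% | 91 vs 96% | 94 vs 99% | about 4-6 |
| 44/40/37% | 72 vs 81% | 71 vs 85% | 74 vs 95% | 9-21 |
| 44/41.5/39% | 37 vs 50% | 33 vs 54% | 31 vs 70% | 12-39 |

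Losses are taken before rounding. The first row is tied to the protocol's own effect: 15 points in one of two equal arms and none in the other averages 15/2 = 7.5 points. The other two rows are illustrative.

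**5. A conditional side effect.** Suppose all three trimesters were stacked, one row per woman per trimester, and a fixed characteristic such as education were tested on those rows. The variance would then be understated by a factor 1 + 2r, and the false-positive rate would be 2[1 − Φ(1.96/√(1+2r))]: 7.4%, 9.8%, 12.1% and 16.6% at r = 0.1, 0.2, 0.3 and 0.5. Whether this applies depends on an analysis choice that the protocol does not state.

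**The case against.** The strongest reply is that the protocol never says these tests will be used across trimesters. The list is generic, it follows a sentence on comparability of the study groups, and for arm comparisons at one visit it raises no within-woman problem. ANOVA is not specified as one-way. This stands as a limit on the wording: no test is assigned to trimester by name. It does not remove the point, because the comparison is a stated objective, no other bivariate test is offered, and the test named for a yes/no outcome is chi-squared.

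A reader might also infer that woman-level factors will be flagged too often. The documents do not support that as a fact. Stacked rows are mentioned nowhere. The list that contains trimester also contains telephone number and patient code, so trimester may only label the visit. General objective 2 seeks factors associated with deficiency in the first three months of gestation, which can mean one row per woman. The Abstract speaks of pregnancy as a whole, so the scope is unclear, but that does not establish stacking.

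Nor is the multilevel regression shown to be wrong: its levels are unstated, a woman level is not excluded, and an article may leave this to the full plan. Clinically relevant variables may enter without passing the bivariate screen. Secondary objective 5, on smoking, is descriptive and promises no test.

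On size, the error is conservative, it touches one element of a secondary objective, and it shrinks with the correlation. At the 7.5-point fall, power is at least 90% either way. All of this stands and limits the weight of the point.

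**Conclusion.** The point holds for the trimester comparison. Followed as written, the plan gives a test whose true level is about 3.6% down to 0.25% instead of 5% for r from 0.1 to 0.5. For r from 0.2 to 0.5, the power lost against a matched test ranges from a few points to 39, depending on the size of the change. The direction holds for any positive within-woman correlation. The amounts rest on an assumed correlation, an assumed pattern of change and 763 complete records. Trimester changes would be missed more often than with a matched test, not as a rule.

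Excess flagging of fixed woman-level factors (about 7% to 17%) would arise only if trimesters were stacked for screening, which the protocol does not state and general objective 2 may exclude. The between-arm comparison and the sample size are unaffected. This is a correction worth making to a secondary analysis, not a threat to the trial's main comparison.

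**What to change.** In the Statistical analysis section, state that comparisons across trimesters use within-woman methods: McNemar (two trimesters) or Cochran's Q (three) for yes/no deficiency, and a mixed model for ioduria and food frequencies. Add that any regression or factor screen pooling more than one trimester includes a random intercept for the woman, nested within care team. Otherwise, fixed woman-level factors should be tested on one row per woman, with the trimester named.

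The cost is wording and slightly more model fitting. Patient code and trimester are already collected, and STATA 10 and HLM6 are already named. No extra data or women are needed.

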## Discussion

One of the strengths of the present study is its design which is pragmatically oriented with respect to the needs of time and material resources.

Another strength of the study is the large number of midwives and patients involved, reinforcing the external validity of the data.

Since no register of women in the first trimester of pregnancy is available, selection of the study population can not be approached with a simple randomised sample but will rather be performed by consecutive sampling which could lead to a selection bias, the self-selection of the volunteer. To determine the possible presence of such a bias the administrative, sociodemographic and obstetric variables of the women who refuse to participate in the study will be analysed.

To increase the validity and reliability of the data collection of the hygienic-dietetic habits by individualised interview, the midwives have been especially trained in this task following a training session prior to initiation of the pilot study and a support investigator will be available to solve any doubts which may arise.

The difficulty in determining iodine intake through diet will be compensated by the determination of iodine levels in urine which is considered a good marker of iodine ingestion according to the WHO, UNICEF and ICCIDD [4,45].

To avoid the phenomenon of contamination which may appear when the intervention influences the subjects in the control group (frequent when the same work centre of the professionals belongs to different study groups), randomisation of the intervention will be performed by the PCN and not by study subjects. Although the unit of randomisation is the primary care unit, the intervention is given at the individual level and the outcomes are also measured at this level. The estimation of the design effect will be taken into account in all the main analyses.

Since participant losses and withdrawals randomly occur, any subject exclusion from the analysis may later affect group comparability. To preserve this all the patients included in the study will be evaluated according to the intention to treat principle and thus, all the patients will be analysed as pertaining to the group to which they were initially assigned independently of the treatment they have actually received.

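### Study group is not exempted from the bivariate significance screen, so the randomised comparison is not guaranteed a cluster-adjusted estimate

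*Protocol article*

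**What the plan says.** The Statistical analysis section of the protocol article first announces a descriptive analysis and a check of baseline comparability. It then names Student's t, Mann-Whitney and ANOVA tests for means, and says that "a Chi- squared test or a Chi -squared tendency test will be done to compare categorical variables". No cluster adjustment is attached to any of these. Next comes a multilevel logistic regression relating the dependent variable to the "independent variables that were statistically significant in the bivariate analysis". The following sentence says that analyses will also be adjusted for potential confounders and clinically relevant variables. The section opens by citing the Consort Cluster guide.

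The Data Collection section gives iodine deficiency as the dependent variable. Its list of independent variables includes study group (intervention or non-intervention), and no sentence exempts study group from the entry rule.

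On clustering, the Sample size calculation states that, "based on an average of 25 pregnant women per PCT, the design effect is 2.2". The Discussion promises: "The estimation of the design effect will be taken into account in all the main analyses".

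**The concern.** The contrast that the trial randomises and is sized for should be estimated whatever its bivariate p-value. Under the rule as written, study group has to earn its place in the only cluster-aware model that the Statistical analysis section names.

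If it fails the screen, the only analysis left for the intervention is an unadjusted one, and the promise in the Discussion is not kept for the central contrast. If it passes, the reported estimate has been selected for being large. The same screen also uses the outcome data to pick other variables for the model.

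The screening test for study group is itself miscalibrated, because women in the same PCT are treated as independent although all of them share one allocation.

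**Working it through.** **Inputs** (Sample size calculation): two-sided alpha of 0.05 and 80% power; 204 women per group before inflation for clustering; a target difference of 15 points; and, for the control rate, "A proportion of iodine deficiency of 44% in the non intervention group is assumed". The section also gives loss to follow-up of 15%, an intracluster correlation (ICC) of 0.05, 25 women per PCT, 898 women and 36 PCTs.

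**The plan's own figures**
- Design effect: 1 + (25 − 1) × 0.05 = 2.2.
- Women: 2 × 204 × 2.2 = 897.6, rounded to 898.
- PCTs: 897.6 / 25 = 35.9, rounded to 36.
- Women per group before clustering: 44% against 29%, with continuity correction, needs 174; 174 / 0.85 = 205, close to the stated 204. So 204 appears to include the 15% loss, which leaves 25 × 0.85 = 21.25 women per PCT for analysis.

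These figures reproduce.

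**Size of an unadjusted test of a variable constant within a PCT.** True size = 2 × (1 − Φ(1.96 / √DE)), where DE is the design effect.
- 25 per PCT: DE = 2.2, √DE = 1.48, 1.96 / 1.48 = 1.32, size 18.6%.
- 21.25 per PCT: DE = 1 + 20.25 × 0.05 = 2.0125, √DE = 1.42, 1.96 / 1.42 = 1.38, size 16.7%.

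A beta-binomial simulation with 36 PCTs gave 18.6% at 25 women per PCT and 17.0% at 21. An unadjusted 95% interval for such a variable would cover about 81-83% and would need to be 1.42 to 1.48 times wider.

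**Woman-level variables.** For a covariate with its own ICC of ρx (assumed, since the article gives none), the design effect is about 1 + 24 × 0.05 × ρx.

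| ρx | design effect | true size |
|---|---|---|
| 0 | 1.00 | 5.0% |
| 0.05 | 1.06 | 5.7% |
| 0.10 | 1.12 | 6.4% |
| 0.20 | 1.24 | 7.8% |
| 0.50 | 1.60 | 12.1% |

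**How often the screen drops study group.** Beta-binomial simulation: 18 PCTs per arm, 21 women each, ICC 0.05, control rate 44%, lower rate in the intervention arm, unadjusted two-sided 5% test. Repeat runs agreed to within about one percentage point on the drop rates.

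| true difference (points) | study group dropped | mean estimate when kept (points) |
|---|---|---|
| 15 | about 5% | 15.5 |
| 10 | about 26% | 12.2 |
| 7.5 | about 46% | 11.2 |
| 5 | about 64% | 9.9 |

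**Does the inflation reach the final test?** A cluster-level t test was used as a stand-in for the multilevel test. Under no effect, about 5% of trials were significant at both stages. Trials significant after cluster adjustment but removed by the screen were 0.00% (to two decimals) at true differences of 0, 5, 7.5, 10 and 15 points.

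**The case against.** The best defence has four parts.

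1. The sentence on confounders and clinically relevant variables is a second route into the model. This stands: a reader might infer that the model admits only variables that pass the screen, and the article does not say that. But the sentence concerns adjustment variables and names none. Study group is the exposure, and nothing there guarantees it a place.

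2. Clustering is addressed by the Consort Cluster citation, the multilevel model and the Discussion. This also stands, so the article cannot be read as ignoring clustering. A general promise does not override a specific entry rule, however; the two need reconciling. The simple tests follow the baseline-comparability sentence, and nothing says that they will supply the reported intervention effect.

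3. The harm is limited. A reader might infer that every screening test runs at 17-19%, or that the final test of the intervention does. Neither is supported. Most screened variables are woman-level (diet, smoking, salt, supplements, age, education) and run at about 5-8% if their ICC is 0.20 or less. A liberal screen also makes study group harder to drop, and the model that follows allows for clustering. What survives is a missing adjusted estimate when the screen fails and an exaggerated one when it passes.

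4. The multilevel sentence speaks of association, which suits general objective 2 on factors associated with deficiency, while the intervention effect is secondary objective 7. That reading is possible. But the sample size is built on the comparison between groups, and the section names no other model for it.

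**Conclusion.** The point holds as a defect in a stated rule. Taken literally, the article makes the cluster-adjusted estimate of the randomised effect conditional on an unadjusted significance test, contrary to its own Discussion.

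At the planned 15-point difference the practical loss is small: study group is dropped about one time in twenty, and the kept estimate is barely distorted. The loss grows if the effect is smaller than planned. The 5- to 10-point differences are illustrative and are not the protocol's assumptions. The 17-19% figure applies to study group, to PCT-level variables, and to midwife-level variables where a PCT has one midwife. It does harm only if a bivariate result is reported as the finding.

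These sizes rest on the plan's ICC of 0.05, 36 equal clusters of 21 to 25 women, a beta-binomial model and, for woman-level variables, assumed covariate ICCs.

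**What to change.** Amend the Statistical analysis section in three places.

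1. State that study group is always in the multilevel model, whatever its bivariate result.
2. Choose the adjustment covariates in advance from baseline variables already collected (first-trimester ioduria is one example) instead of by bivariate significance. The full list can sit in the statistical analysis plan.
3. State that any reported comparison by study group, PCT-level variable or midwife-level variable uses a cluster-adjusted test and interval, so that this section agrees with the Discussion.

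The choice of estimator can be left to the analysis plan. The cost is analysis wording and somewhat wider intervals for those comparisons: up to about 1.4 to 1.5 times the unadjusted width for variables constant within a PCT. No new data, participants or procedures are needed.
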